**LIST OF ABBREVIATIONS AND RELEVANT DEFINITIONS**

|               |                                                                                                                                                                                                                                                                                                                                           |
|---------------|-------------------------------------------------------------------------------------------------------------------------------------------------------------------------------------------------------------------------------------------------------------------------------------------------------------------------------------------|
| AE            | Adverse Event                                                                                                                                                                                                                                                                                                                             |
| ApoA-I        | Apolipoprotein A-I                                                                                                                                                                                                                                                                                                                        |
| ApoB100       | Apolipoprotein B100                                                                                                                                                                                                                                                                                                                       |
| CCMO          | Central Committee on Research Involving Human Subjects; in Dutch: Centrale Commissie Mensgebonden Onderzoek                                                                                                                                                                                                                               |
| CV            | Curriculum Vitae                                                                                                                                                                                                                                                                                                                          |
| DMII          | Diabetes Type 2                                                                                                                                                                                                                                                                                                                           |
| GCP           | Good Clinical Practice                                                                                                                                                                                                                                                                                                                    |
| GMP           | Good Manufacturing Practice                                                                                                                                                                                                                                                                                                               |
| HDL-C         | High-density lipoprotein cholesterol                                                                                                                                                                                                                                                                                                      |
| hsCRP         | High-sensitive C-reactive protein                                                                                                                                                                                                                                                                                                         |
| IL-6          | Interleukin-6                                                                                                                                                                                                                                                                                                                             |
| MCP-1         | Monocyte chemotactic protein-1                                                                                                                                                                                                                                                                                                            |
| METC          | Medical research ethics committee (MREC); in Dutch: medisch ethische toetsing commissie (METC)                                                                                                                                                                                                                                            |
| (S)AE         | (Serious) Adverse Event                                                                                                                                                                                                                                                                                                                   |
| sE-Selectin   | Soluble E-Selectin                                                                                                                                                                                                                                                                                                                        |
| sICAM-1       | Soluble Intercellular adhesion molecule 1                                                                                                                                                                                                                                                                                                 |
| Sponsor       | The sponsor is the party that commissions the organisation or performance of the research, for example a pharmaceutical company, academic hospital, scientific organisation or investigator. A party that provides funding for a study but does not commission it is not regarded as the sponsor, but referred to as a subsidising party. |
| TAG           | Triacylglycerol                                                                                                                                                                                                                                                                                                                           |
| TBARS         | Thiobarbituric acid reactive substances                                                                                                                                                                                                                                                                                                   |
| TCH           | Total cholesterol                                                                                                                                                                                                                                                                                                                         |
| TNF- $\alpha$ | Tumor necrosis factor alpha                                                                                                                                                                                                                                                                                                               |
| TNFR          | Tumor necrosis factor receptor                                                                                                                                                                                                                                                                                                            |
| VCAM-1        | Vascular cell adhesion molecule 1                                                                                                                                                                                                                                                                                                         |
| Wbp           | Personal Data Protection Act (in Dutch: Wet Bescherming Persoonsgegevens)                                                                                                                                                                                                                                                                 |
| WMO           | Medical Research Involving Human Subjects Act (in Dutch: Wet Medisch-wetenschappelijk Onderzoek met Mensen)                                                                                                                                                                                                                               |

## SUMMARY

**Rationale:** Plant sterols can oxidize, which results in the formation of oxyphytosterols. Animal studies have now suggested that oxyphytosterols are atherogenic, but this relation has not yet been studied in humans. In our previous study (METC 09-3-088) we have shown in healthy volunteers that serum oxyphytosterol concentrations are linked to oxidative stress status (i.e. we were able to identify high and low sterol oxidizers). Type II diabetic patients are characterized by increased oxidative stress markers and reduced antioxidant capacity. Therefore, we want to evaluate the oxyphytosterol concentrations in this population. Moreover, we propose to evaluate the effect of antioxidant supplementation, i.e. vitamin E or lipoic acid, on serum oxyphytosterol concentrations in type II diabetic patients. Lowering oxyphytosterol concentrations in this population would obviously be beneficial in case oxyphytosterols turn out to be atherogenic.

**Objective:** The objective of the present study is to examine the effect of consuming vitamin E (900 mg) or lipoic acid (600 mg) for 4 weeks on fasting oxyphytosterol concentrations in type II diabetic patients.

**Study design:** A randomized, double blind, placebo-controlled crossover design. The total study duration will be 20 weeks, consisting of 3 test periods of 4 weeks in which subjects will use the investigational products. Each period will be separated by a washout period of 4 weeks.

**Study population:** 20 diabetic male and female patients, aged 18-75 years.

**Intervention:** Subjects will be asked to consume three times daily control capsules, vitamin E capsules (total 900 mg) or lipoic acid capsules (total 600 mg) for three periods of four weeks. They will be asked to consume these capsules daily, divided over three eating moments. Each test-period is separated by a washout period of 4 weeks, during which the subjects will return to their habitual dietary patterns. They are not allowed to consume any dietary supplements during the entire study, including the washout periods. In total they will visit the department on 9 occasions to give a blood sample.

**Main study parameters/endpoints:** Blood samples will be drawn at weeks 1, 3 and 4 of each test period. The samples will be analysed for serum / plasma concentrations of plant sterols, oxyphytosterols, oxidative stress markers, antioxidant capacity, lipoproteins, and for markers reflecting low-grade systemic inflammation and endothelial dysfunction.

**Nature and extent of the burden and risks associated with participation, benefit and group relatedness:** Blood samples will be drawn on 9 different occasions in a time frame of 20 weeks with a total amount of 130.5 mL. During the screening procedure 11 mL (2x 5.5 ml) blood will be sampled. Furthermore, subjects will be asked to fill out a food frequency questionnaire three times at the end of each experimental period. Apart from a

haematoma or bruise, which can occur during or after venepuncture, no side effects of the intervention itself are expected.

## 1. INTRODUCTION AND RATIONALE

### 1.1 Oxyphytosterols

Oxyphytosterols are the oxidized form of plant sterols in the circulation. Plant sterols are normal components in our daily diet and they exert the same cellular functions in plants as cholesterol does in animals. The average intake of plant sterols in Western countries is approximately 250 mg/day, mainly derived from vegetable oils, cereals, nuts, seeds, fruits and vegetables. Plant stanols are the saturated derivatives of plant sterols. Plant sterols and stanols are structurally related to cholesterol, but they have a different side-chain configuration. As humans are unable to synthesize plant sterols and stanols, their serum concentrations are mainly determined by intestinal absorption and due to their low absorption; serum concentrations are less than 1% of that of serum cholesterol (1,2).

As mentioned above, plant sterols and cholesterol are structurally related, and therefore both can be oxidized and give rise to oxidation products. The side-chain of cholesterol can be oxidized enzymatically and the nucleus non-enzymatically, which is probably a radical driven process. For plant sterols, only the nucleus can be oxidized. Due to sterical hindrance caused by the different side-chain structure of plant sterols as compared to cholesterol, the side-chain of plant sterols cannot be oxidized. The ring-oxidation products are potentially atherogenic, at least for cholesterol oxidation products (3). The most important oxyphytosterols that have been identified are;  $5\alpha,6\alpha$ -epoxy-sitosterol,  $7=O$ -sitosterol,  $7\beta$ -OH-sitosterol, en  $3\beta,5\alpha,6\beta$ -tri-hydroxy-sitosterol. The same oxyphytosterols can be identified for campesterol (4). Research concerning the location where oxyphytosterols are produced, on the breakdown route and speed or on the pathophysiological effect, is still lacking unfortunately.

The concentrations of oxyphytosterols in human plasma have so far been measured in two cross-sectional studies and in two intervention studies. In a first study by Plat et al. (4) oxyphytosterols could be identified in serum of sitosterolaemic patients, but not in serum from healthy volunteers. Later, Grandgirard et al. used a quantification method with a lower limit of detection and were able to identify concentrations of oxyphytosterols in plasma from healthy volunteers (5). In the mean time the methodology to analyse serum oxyphytosterol concentrations has much improved. We have recently determined serum oxyphytosterol concentrations in 45 healthy human subjects, who consumed 3.0 g/d plant sterols and plant stanols as part of their daily diet for 4 weeks (METC 09-3-088). Results of this study indicated that neither daily consumption of a plant sterol-enriched margarine

nor a plant stanol-enriched margarine changed oxyphytosterol concentrations when compared to control margarine. However, additional analyses in this study showed that oxyphytosterol concentrations were highly correlated with oxidized LDL concentrations and oxysterol concentrations, which are both sensitive markers for oxidative stress. Interestingly, we were able to identify consistent high and low sterol oxidizers. This is of course a highly relevant finding in the light of potential atherogenicity of oxyphytosterols.

## **1.2 Oxidative stress and diabetes**

Oxidative stress is defined as an increased production of reactive oxygen species (ROS) and/or reduced antioxidant capacity and is thought to play a central role in the development of atherosclerosis and plaque formation (6,7). Reducing oxidative stress by means of antioxidants has major health benefits and is associated with a lower rate of coronary heart disease (8,9). Several chronic diseases such as diabetes mellitus type 2 (DMII) are characterized by an increased oxidative stress status (10).

DMII is one of the leading chronic diseases worldwide and a major risk factor for the development of cardiovascular diseases. Oxidative stress is associated with the development and progression of diabetes and its complications (11). Studies have shown that DMII patients have elevated serum oxysterol concentrations (cholesterol oxidation products) when compared to healthy subjects (12, 13). Due to the similarity in structure between oxysterols and oxyphytosterols and the correlation between serum oxysterols and oxyphytosterols, we would expect that DMII patients would also have elevated serum oxyphytosterol concentrations. This has however never been evaluated, but is relevant knowledge since in vitro studies and animal studies have shown that oxyphytosterols themselves might exert atherogenic properties, highlighting the importance of reducing serum oxyphytosterol concentrations (14,15).

## **1.3 Vitamin E and lipoic Acid**

As mentioned above, consumption of antioxidant supplements is able to reduce oxidative stress and might eventually lower CVD. Vitamin E is one of the most well known dietary antioxidants and studies have shown that consuming vitamin E, results in reduced oxidative stress markers (16,17). While previous research has shown that serum oxysterol concentrations can be reduced via vitamin E consumption (18), the effect on serum oxyphytosterol concentrations has never been evaluated. Besides vitamin E other antioxidants also received a lot of attention. Evidence is emerging concerning the beneficial effects of lipoic acid. Lipoic acid is a short chain fatty acid that is present in nature and produced endogenously in mammals, where it has a role as a cofactor for

mitochondrial  $\alpha$ -ketoacid dehydrogenases. It has strong antioxidant capacities and has been shown to reduce oxidative stress in humans (19). In addition, lipoic acid is able to increase insulin sensitivity in DMII patients and to alleviate diabetic neuropathy (20,21) and is available as dietary supplement. Vitamin E is a fat-soluble antioxidant while lipoic acid is both water-soluble and fat-soluble. To increase the knowledge of oxyphytosterols as an oxidative stress marker, it is relevant to compare two antioxidants that differ regarding their solubility, i.e. vitamin E and lipoic acid.

In our previous study, we have shown that serum oxyphytosterol concentrations are strongly linked to oxidative stress status. By evaluating the effect of antioxidant supplementation on serum oxyphytosterol concentrations, the role of oxyphytosterols as oxidative stress makers will be confirmed. We want to evaluate this effect in DMII patients, as this population is characterized by increased oxidative stress markers and reduced antioxidant capacity.

## 2. OBJECTIVES

The objective of the present study is to examine the effect of consuming vitamin E (900 mg/day) or lipoic acid (600 mg/day) for 4 weeks on fasting oxyphytosterol concentrations in DMII patients.

The null hypothesis ( $H_0$ ) is:

In DMII patients, consuming vitamin E (900 mg) or lipoic acid (600 mg) for 4 weeks does not change oxyphytosterol concentration as compared to a control condition.

The alternative hypothesis ( $H_a$ ) is:

In DMII patients, consuming vitamin E (900 mg) or lipoic acid (600 mg) for 4 weeks changes oxyphytosterol concentration as compared to a control condition.

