#### 4.5 Sample size calculation

In our previous study, we were able to detect a decrease of 0.07 ng/mL in 7b-OH-campesterol concentrations in healthy volunteers upon plant stanol consumption. A larger decrease in oxyphytosterol concentrations is expected upon vitamin E and lipoic acid consumption, as they are antioxidants and research has already shown that they are able to decrease oxidative stress markers. A recent study found a decrease of 28% in oxysterol concentrations upon vitamin E consumption [18]. We would expect larger decreases upon vitamin E and lipoic acid consumption in DMII patients, as they are characterized by an increased oxidative stress status and changes will be larger if baseline concentrations are higher. Therefore, we would expect a change of 0.15 ng/mL in plasma 7b-OH-campesterol concentrations in DMII patients. Using this true change of 0.15 ng/mL and the known within-subject variation on the response of 0.14 ng/mL, it can be calculated that we need 18 subjects to have a power of 80% to detect the indicated difference, if we consider a P-value < 0.017 (to account for multiple comparisons between

groups) to be statistically significant. The expected dropout rate is 10%. Therefore, 20 diabetic patients will be recruited.

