#### 6.1.1 Metabolic risk markers

- Oxidative stress markers

Butylated hydroxy toluene (BHT) will be added to the EDTA blood collection tubes to prevent auto-oxidation of the sterols and other components in the blood.

The following oxidative stress markers will be determined in plasma:

- Plasma oxyphytosterol concentrations, measured in week 1, 4, 9, 12, 17 and 20
- Plasma oxysterol concentrations, measured in week 1, 4, 9, 12, 17 and 20
- Plasma oxidized LDL concentrations, measured in week 1, 4, 9, 12, 17 and 20
- TBARS assay, measured in week 1, 4, 9, 12, 17 and 20

- Antioxidant capacity

The following antioxidant concentration will be measured to determine compliance of the subjects and to determine antioxidant capacity:

- Plasma vitamin E concentrations, measured in week 1, 4, 9, 12, 17 and 20
- Plasma lipoic acid concentrations, measured in week 1, 4, 9, 12, 17 and 20
- Glutathion concentrations, measured in week 4, 12 and 20
- Plasma uric acid concentrations, measured in week 4, 12 and 20
- Trolox antioxidant capacity, measured in week 4, 12 and 20

- Lipid and lipoprotein concentrations

The following lipid and lipoprotein concentrations will be measured to assess determinants of the lipid metabolism:

- TCH concentrations, measured in week 1, 3, 4, 9, 11, 12, 17, 19 and 20
- HDL-C concentrations, measured in week 1, 3, 4, 9, 11, 12, 17, 19 and 20

- TAG concentrations, measured in week 1, 3, 4, 9, 11, 12, 17, 19 and 20
  - ApoB100 concentrations, measured in week 1, 3, 4, 9, 11, 12, 17, 19 and 20
  - ApoA-1 concentrations, measured in week 1, 3, 4, 9, 11, 12, 17, 19 and 20
- Glucose metabolism
    - Glucose concentrations, measured in week 4, 12 and 20
  - Low-grade inflammation and endothelial activity

The following parameters will be measured to assess concentrations of low-grade inflammation and endothelial activity:

- hsCRP, TNF- $\alpha$ , TNF-RI, TNFR-II, IL-6, MCP-1, sICAM-1, sVCAM-1 and sE-selectin, measured in week 4, 12 and 20
- Iron and copper status
- The following markers will be measured to assess iron and copper status. Iron and copper are the main metals present in human sera, and an increased metal status could indicate a higher oxidative susceptibility.
- Total iron, measured in week 4, 12 and 20
  - Transferrine, measured in week 4, 12 and 20
  - Ferritine, measured in week 4, 12 and 20
  - Copper, measured in week 4, 12 and 20
  - Ceruloplasmin, measured in week 4, 12 and 20

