### **8.2 Univariate analysis**

Differences between the two experimental periods and the control period will be calculated and effects of the intervention will be examined by analysis of variance (ANOVA) test. A p-value <0.017 is considered to be statistically significant. All statistical analyses will be performed using SPSS 18.0 for Mac Os X (SPSS Inc., Chicago, IL, USA).

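### No single oxyphytosterol or sum is named as primary, and the 0.017 threshold allows only for comparisons between treatments, so the false-positive rate for the main objective is uncontrolled across compounds

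*Protocol*

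**What the plan says.** - **Hypothesis (section 2).** The null is that either supplement "does not change oxyphytosterol concentration as compared to a control condition". No compound, total or time point is given beyond four weeks of intake.
- **What the term covers (section 1.1).** The text introduces four sitosterol oxidation products with "The most important oxyphytosterols that have been identified are" and adds: "The same oxyphytosterols can be identified for campesterol".
- **Endpoint list (section 6.1.1).** The entry is "Plasma oxyphytosterol concentrations, measured in week 1, 4, 9, 12, 17 and 20". The Summary's main endpoints are a long list of marker groups without a primary one, and Table 3 in section 6.3 has one undivided oxyphytosterol line per sampling visit.
- **Sample size (section 4.5).** Here one compound appears: "we would expect a change of 0.15 ng/mL in plasma 7b-OH-campesterol concentrations in DMII patients". The variability used is "the known within-subject variation on the response of 0.14 ng/mL". The result is 18 subjects for 80% power at P < 0.017, with 20 recruited. The reason given for 0.017 is the comparisons between treatment groups.
- **Analysis (section 8.2).** Each of the two supplement periods is set against control by ANOVA, and "A p-value <0.017 is considered to be statistically significant". Nothing is said about handling more than one oxyphytosterol.

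**The concern.** The hypothesis, the power statement and the significance threshold do not refer to the same variable. The hypothesis is about a class, the power is about one member of it, and the threshold is spent entirely on treatment comparisons. A significant result on any member could be reported as meeting the objective, and the protocol has no rule against it.

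The protocol itself shows how the conclusion can turn on this. Section 1.1 reports that in the team's earlier margarine study neither the sterol nor the stanol product altered oxyphytosterol concentrations relative to control. Section 4.5 says that in the previous study a fall of 0.07 ng/mL in 7b-OH-campesterol was detected with plant stanols. These appear to be the same study, although section 4.5 does not give its number. If so, one data set supported both a class-level answer of no change and a single-compound answer of a decrease. Under the present hypothesis either could be presented as the main result of this trial.

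**Working it through.** **1. The plan's own sample size.** Inputs from section 4.5: difference 0.15 ng/mL, within-subject SD 0.14 ng/mL, threshold 0.017 (taken as two-sided), power 80%. If 0.14 is the SD of a single measurement, the SD of a within-subject difference is 0.14 × √2 = 0.198.

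n = ((z₀.₉₉₁₅ + z₀.₈₀) × 0.198 / 0.15)² = ((2.387 + 0.842) × 1.320)² = 18.2

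Power at n = 18 by the same approximation is 79.6%, so the stated 18 is reproduced closely. (Taking 0.14 as the SD of the difference would give 9.1.) The calculation contains one compound, so the 80% describes 7b-OH-campesterol and nothing else.

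**2. What 0.017 pays for.** 0.05 / 3 = 0.0167, stated as 0.017. Three treatments have three pairwise comparisons, so the whole allowance is used within one variable. For one variable, treating the comparisons as independent:

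- two comparisons with control: 1 − (1 − 0.017)² = 3.4%
- all three pairwise comparisons: 1 − (1 − 0.017)³ = 5.0%

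The comparisons share data, so the true figures are slightly lower. Simulation gives 3.2% and 4.7%. For one named endpoint the threshold does its job.

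**3. What happens with several compounds.** Two inputs are assumptions. For the number of compounds, eight would be the four sitosterol products plus the same four for campesterol, and four is a smaller case for comparison. The protocol gives no correlation between compounds, so the range 0 to 0.95 is shown. The decision rule examined is that each compound is tested at 0.017 and any one result suffices.

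Formula check at zero correlation, eight compounds, two comparisons with control: 1 − (1 − 0.017)¹⁶ = 24.0%. This ignores the shared control period.

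Simulated error with no true effect, two comparisons with control (18 completers, three-period crossover, paired t tests at two-sided 0.017, equal correlation between compounds, 20,000 runs):

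| Correlation | 4 compounds | 8 compounds |
|---|---|---|
| 0 | 12.1% | 23.0% |
| 0.3 | 11.5% | 20.7% |
| 0.5 | 11.1% | 18.9% |
| 0.7 | 9.6% | 14.5% |
| 0.8 | 8.3% | 11.8% |
| 0.9 | 6.5% | 9.5% |
| 0.95 | 5.5% | 6.9% |

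The range is therefore about 7 to 24% for eight compounds (23% simulated and 24% by formula at the top) and about 6 to 12% for four.

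**4. Cost of correcting across everything.** Eight compounds by three comparisons is 24 tests, and 0.05 / 24 = 0.0021. Putting that threshold into the formula in step 1 gives n = 26.8, so about 27 evaluable subjects. Power at 18 falls to about 55%. With only the 16 comparisons against control, 0.05 / 16 = 0.0031, n = 25.1 and power at 18 is about 60%.

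**The case against.** The strongest reply is that nothing in the protocol prescribes testing compound by compound with any one result sufficing. The hypothesis is worded in the singular, which also fits a total, or the one compound used for sizing. Under either reading the error is 3.2 to 4.7% and 0.017 is adequate. This stands: the defect is an unspecified primary variable, not a demonstrated error rate. It does not remove the point, because the protocol never says which reading applies. Naming the primary variable is protocol content, so a separate analysis plan would not excuse its absence here.

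A reader might infer that eight compounds will be measured. The documents do not support that as fact. The count comes from background text on what has been identified, and neither section 6.1.1 nor Table 3 lists the compounds to be assayed.

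A reader might also put the error at about 30%. Simulation gives 31% only for eight uncorrelated compounds with all three pairwise comparisons. The third comparison, vitamin E against lipoic acid, belongs neither to the hypothesis in section 2 nor to the comparisons with control in section 8.2. The high figures also need weak correlation, which the protocol neither states nor excludes.

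Finally, section 8.2 could be read as one overall ANOVA per variable at 0.017. Eight such tests give about 4 to 13%, and the low end is within 5%.

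**Conclusion.** The point holds as a failure to designate the primary endpoint. The hypothesis concerns a class, the power concerns one compound, and the threshold adjusts only for treatment comparisons, so the error for the main objective has no stated bound across compounds.

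Its size depends on the number of compounds, their correlation and the decision rule, none of which the protocol states. For the two comparisons with control, under the any-one-suffices rule, every multi-compound case in the table lies above 5%. With one named compound the error is below 5% even when all three contrasts are counted. No single figure should be quoted as the trial's error rate. What can be said is that the protection that 0.017 was meant to give is secured only if one variable carries the conclusion.

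**What to change.** Amend three sections:

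- **Section 2:** word the hypotheses for plasma 7b-OH-campesterol, the compound the trial is sized on.
- **Section 6.1:** name plasma 7b-OH-campesterol at the end of each period (weeks 4, 12 and 20) as the single primary endpoint. List the other oxyphytosterols to be assayed and label them secondary.
- **Section 8.2:** state that the objective is judged on the primary endpoint only, at 0.017, and that results for the other compounds are supportive.

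The sample size, the visits and the threshold do not change. The cost is wording, plus one real restriction: a positive result on another oxyphytosterol can no longer be claimed as the main result. The change should be made before the treatment code is broken.

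A Holm or Bonferroni correction over all compounds and contrasts is not a comparable alternative. Holm's first step uses the same 0.05 / 24 threshold as in the working, where 18 subjects give about 55% power instead of 80%.
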